## Abstract

**Background:**

Neck pain is a prevalent global musculoskeletal issue, significantly contributing to the loss of years of healthy life due to disability. Chronic nonspecific neck pain (CNNP) involves diverse symptoms impacting mobility and quality of life. While therapeutic exercises demonstrate efficacy, the role of photobiomodulation therapy (PBMT) remains uncertain. This study aims to assess the additional effects of PBMT within a multimodal therapeutic intervention for CNNP.

**Methods:**

A randomized, two-arm, controlled, blind clinical trial follows CONSORT and SPIRIT guidelines. Participants diagnosed with CNNP will receive a stand-alone multimodal therapeutic intervention or the same program with additional PBMT. The primary outcomes will be assessed by the functional disability identified through applying the NDI (Neck Disability Index). Secondary outcomes will be pain intensity during rest and active neck movement, catastrophizing and kinesiophobia, functionality, and disability assessed at baseline, after 8 weeks, and at a 4-week follow-up. Both groups receive pain education before personalized interventions, including resistance exercises, neuromuscular activities, mobility, and body balance. The PBMT group undergoes low-level light therapy. Intention-to-treat analysis, using linear mixed models, employs data presented as mean, standard deviation, and differences with a 95% confidence interval. Non-normally distributed variables transform. Statistical significance is set at 5%.

**Discussion:**

This study addresses a critical gap in understanding the combined effects of PBMT and therapeutic exercises for CNNP. The findings aim to guide clinicians, researchers, and CNNP sufferers through rigorous methodology and diverse outcome assessments, offering valuable insights into evidence-based practices for CNNP management. Data confidentiality is maintained throughout, ensuring participant privacy during statistical analysis.

**Trial registration:**

Effects of adding photobiomodulation to a specific therapeutic exercise program for the treatment of individuals with chronic nonspecific neck pain, registration number: NCT05400473, on 2022-05-27.

**Supplementary Information:**

The online version contains supplementary material available at 10.1186/s13063-024-08289-1.

## Background

Globally, in 2020, it was estimated that around 494 million people had at least one musculoskeletal disorder [1]. Among these disorders, neck pain is one of the most prominent, with 22.1 million years of healthy life lost due to disability (YLDs) [2]. With a notable incidence in adult women and among individuals aged between 39 and 69 years, neck pain is responsible for 2.6 of YLDs of the global total [2].

Due to the vast magnitude of epidemiological reports related to neck pain. It is noted that it is a clinically diverse condition, marked by persistence and recurrence, most often characterized as chronic nonspecific neck pain (CNNP). Varying in intensity, location, and irradiation pattern among affected individuals, CNNP frequently results in functional limitations that impair quality of life, compromising mobility and the performance of daily living activities, in addition to emotional aspects, such as stress and anxiety, which contribute to the sensitization of the nervous system and the amplification of pain perception. In this way, all these components only confirm the considerable socioeconomic impacts of the CNNP on the loss of productivity, the increase in sick leave, and the financial costs of health care linked to its consequences [3–5].

All this complexity of signs, symptoms, and impairments is linked to CNNP. Several therapeutic approaches are suggested and tested in this scenario; for example, self-education interventions improve pain intensity, disability, kinesiophobia, and catastrophizing [6]. However, over the last few years, several studies have consolidated therapeutic exercises as a possible preventive intervention when the objective is to reduce the risk of an episode of neck pain. As the first line of treatment, with a frequency of at least three times a week, the aim is to improve function and pain in CNNP [7–10].

Even though no exercise is superior to others, there is significant variation in the methodological quality of the studies [11]. Therapeutic exercises involving resistance, mindfulness-based, and motor control are practical in promoting improvement in neck pain [12]. The frequency and duration of sessions are suggested to improve pain significantly during exercise, especially involving motor control [10]. Furthermore, when they include strengthening the cervical extensor muscles, they promote a reduction in neck pain and disability, using low and/or high loads, elastic resistance, and individualized therapeutic plans [13, 14].

In this context, several other resources have been tested for the consequences linked to CNNP. Over the last few years, photobiomodulation therapy (PBMT) has emerged and characterized as a light irradiation therapy that uses low-level laser therapy (LLLT) (light amplification by stimulated emission of radiation) and/or LEDs (light-emitting diodes) from the visible to the infrared spectrum, which, when interacting with tissues, promotes the release of growth factors related to epithelial cells, fibroblasts, and collagen proliferation. Furthermore, modulation of cellular behavior is characterized by the production of mitochondrial ATP and increased cellular metabolism, potential angiogenesis, and collagen synthesis. Physiological effects that potentially explain the clinical effects of using PBMT in tissue repair and reducing pain intensity [15].

Despite the cellular effects and consolidated mechanisms of action regarding using PBMT, the same does not occur when analyzing the results of the last five systematic reviews published between 2009 and 2022 involving its clinical use in CNNP [16, 17], which demonstrated that LLLT reduces pain up to 22 weeks after completion of treatment. The evidence does not support a safe conclusion about use [18–21].

In contrast, it indicates that using LLLT can benefit pain, function, and quality of life. Also, it suggests that the association of PBMT with therapeutic exercises seems to promote significant benefits only for pain intensity, highlighting that the combined use of these resources in individuals with CNNP does not seem to encourage a minimally effective clinical difference [19–22], and indicates that LLLT reduces neck pain, improves range of motion and pain pressure threshold, and can be used with other interventions such as manual therapy and therapeutic exercise.

In this context, the present study is justified, considering the complexity and high prevalence of CNNP, the lack of solidity in clinical findings related to the use of PBMT associated with therapeutic exercises, and the general recommendation of previously published systematic reviews, indicating the carrying out of new clinical trials following appropriate clinical guidelines and methodological processes. Therefore, the objective of this study will be to evaluate the additional effects of including PBMT in a multimodal therapeutic intervention program for individuals with CNNP. The structured hypothesis for the study is that the inclusion of PBMT in a multimodal therapeutic intervention program will improve functionality and disability, pain intensity, catastrophizing, kinesiophobia, and perception of the global effect of the treatment more than the use of a multimodal therapeutic intervention program alone in individuals with CNNP.

## Methods and design

### Design and setting

This will be a randomized, two-arm, controlled, and blind clinical trial. The research project’s methodology will be based on the methodological standards established by the CONSORT Statement [23]. In addition, the clinical trial protocol will follow the recommendations of the SPIRIT Statement (Standard Protocol Items: Recommendations for Interventional Trials (Table 1) [24]. The Template for Intervention Description and Replication (TIDieR) checklist will be used to describe and replicate interventions better [25].

**Table 1 Tab1:**
[figure not shown]
Schematic diagram of Spirit Statement overall study schedule

*−t1* time of recruitment of research participants, *T1* Evaluation 1, *T2* Phase 1 (4 weeks of intervention), *T3* Phase 2 (4 weeks of intervention), *T4* Evaluation 2, *T5* Evaluation 3, *PMIT*: Multimodal therapy Intervention Programme, *PMIT+PBMT* Multimodal therapy Intervention Programme+photobiomodulation therapy, *NDI* Neck Disability Index, *END* Numerical pain scale, *TAMPA* Kinesiophobia Tampa Scale, *EPC* Catastrophic Thoughts Scale

The research will be carried out in the movement laboratory at the University Nove de Julho, São Paulo, Brazil. It will be disseminated through posters, lectures in public health units, and consultations with the waiting list of rehabilitation clinics in São Paulo.

This study was approved by the Research Ethics Committee of University Nove de Julho nº 58616022.1.0000.5511 and was prospectively registered on the Clinical trials platform under number NTC05400473.

Participant recruitment began in July 2022 and is expected to continue until July 2025 (Table 1).

### Recruitment and participants

The sample calculation was processed using the Ene software, version 3.0 (Autonomous University of Barcelona, Spain). Therefore, functional disability measured using the Neck Disability Index (NDI) was chosen as the primary outcome variable. The calculation was based on detecting differences of 7 points between the groups, assuming a standard deviation of 7 [26, 27]. Thus, considering a statistical power of 80% and an alpha of 5%, a minimum number of 30 individuals per group was estimated.

Individuals with chronic nonspecific neck pain, defined as pain in the posterior cervical region between the superior nuchal line and the first thoracic spinous process and/or shoulder girdle, both genders, aged between 18 and 65 years, with neck pain for more than 90 days, NDI score ≥ 5, and Numerical Pain Scale (NPS) score ≥ 3 at rest or during active cervical movement [28, 29]. The exclusion criteria adopted in the present study will be neck pain associated with nerve root involvement (measured by clinical examination of dermatomes, myotomes, and reflexes), previous spine surgery, patients treated with physiotherapy for neck pain in the last 3 months to the study, spinal severe disorders such as fractures, tumors, inflammatory, and infectious diseases, any contraindication to low-power laser therapy, rheumatic, metabolic, neurological, or cardiopulmonary diseases, patients requiring artificial cardiac pacemakers, patients with deficits sensory, skin diseases, especially at the site of the current application, and history of tumors or cancer in the last 5 years [28, 29].

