### Neck Disability Index (NDI)

The NDI is a validated instrument for the Brazilian population, comprising ten questions investigating disability and neck pain. Responses are scored from 0 to 5, and the total score ranges from 0 to 50 points, based on the answers to assess the degree of disability due to neck pain. It has been previously validated and translated for the Brazilian population and reported a clinically important minimal difference of seven points out of the possible 50 for individuals with neck pain [26, 29, 30].

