## Statistical analysis

Continuous and categorical variables will be described as mean ± SD (or median)) and frequency (%). After evaluating the normality distribution using the Kolmogorov-Smirnov test, parametric or non-parametric methods will be used. To check the quality of randomization and find potential confounders in the univariate analysis, statistical tests such as the chi-square test, one-way ANOVA, and Kruskall Wallis test (with Bonferroni post hoc test (if necessary)) are used. Regarding the main effects, linear mixed models will be applied for variables with normal distribution, considering the interaction between the factors time (before interventions, after 08 sessions, and 4-week follow-up) and groups. The data will be presented as mean, standard deviation, and the difference between means, and a 95% confidence interval of these differences. Sensitivity analysis will assess the missingness mechanism, and the data analysis approach will be the intention-to-treat method. All analyses will be done using SPSS version 26 (Chicago, IL, USA), and the significance level for all tests will be 5% [40].

Furthermore, Cohen *d* will be calculated to identify the effect size between the groups. The following interpretation of the Cohen *d* value will be used as a basis: around 0.2 (weak), around 0.5 (moderate), and above 0.8 (strong) [40].

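### The stated minimum of 30 per group does not follow from the printed inputs, which give 17 per group; at 30 the power for 7 points is about 97%, not 80%

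*Protocol article*

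**What the plan says.** The sample-size paragraph is in the Protocol article, section Recruitment and participants. It names the NDI as the outcome on which the trial is sized: "functional disability measured using the Neck Disability Index (NDI) was chosen as the primary outcome variable". The effect and variability follow: "The calculation was based on detecting differences of 7 points between the groups, assuming a standard deviation of 7". The result is given as: "considering a statistical power of 80% and an alpha of 5%, a minimum number of 30 individuals per group was estimated".

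The section Neck Disability Index (NDI) explains the choice of 7, citing a "clinically important minimal difference of seven points out of the possible 50".

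The 30 is a per-group figure, not a total. The two intervention sections each describe a group of 30, and the section on allocation, randomization and blinding has 60 numbered envelopes with 1:1 allocation. The sample-size paragraph mentions no dropout allowance, multiplicity correction, change-score variance or sidedness.

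**The concern.** The paragraph prints a complete set of inputs and presents 30 as their direct result. A 7-point difference with an SD of 7 is a full standard deviation, a large effect, and 30 per group is well above what such an effect needs at 80% power. So at least one printed figure is not the one used, or a step between inputs and result is missing.

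This is the only justification the article gives for the size of the trial. If the figures cannot be reproduced, a reader does not know what effect the trial was designed to detect, at what power, or whether the number allows for participants who do not complete 8 weeks of treatment and a further 4 weeks of follow-up.

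**Working it through.** **Inputs** (Protocol article, Recruitment and participants, unless noted)
- Difference δ = 7 NDI points
- Standard deviation σ = 7
- Power 80%, alpha 5%
- Two groups, 1:1 (Treatment allocation, randomization, and blinding)
- Sidedness is not stated; two-sided is assumed, and one-sided is also tried

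**Step 1: try to reproduce 30 per group**

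Normal approximation, per group:

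n = 2 (z₀.₉₇₅ + z₀.₈₀)² σ²/δ² = 2 × (1.960 + 0.842)² × 49/49 = 2 × 7.849 = 15.7, so 16.

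The t-test (noncentral t, d = 7/7 = 1.0) gives 16.7, so 17. Power is 78.1% at 16 per group and 80.7% at 17. One-sided, the results are 13 (normal) and 14 (t-test).

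None of these is near 30.

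**Step 2: what 30 per group gives on the printed inputs**

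- Noncentrality = δ / (σ√(2/n)) = 1.0 × √(30/2) = 3.873.
- Power for 7 points = 96.8% by t-test (97.2% by normal approximation).
- The standardised effect detectable with 80% power at 30 per group is 0.736. At SD 7 that is 0.7356 × 7 = 5.15 points. For a 7-point difference it is an SD of 7/0.7356 = 9.5.

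**Step 3: could an unreported variant explain 30?**

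| Variant (otherwise the printed inputs, two-sided t-test) | n per group |
|---|---|
| Power 90% | 23 |
| Power 95% | 27 |
| Alpha divided by 7 | 27 |
| 17 inflated for 10% / 20% / 30% / 40% dropout, n/(1−d) | 19 / 22 / 25 / 29 |
| Rank-test efficiency loss (0.955 to 0.864) | 18 to 20 |
| Change score, zero correlation, SD 7√2 = 9.9 | 33 (32 by normal approximation) |

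Dropout alone would have to be 1 − 17/30 = 43% to move 17 to 30. A change score with SD 7 at each visit has SD 7√(2(1−ρ)). It reaches about 9.5, and hence 30 per group, when ρ is about 0.08: 7 × √(2 × 0.92) = 9.5. The article states none of these adjustments.

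**Step 4: why the cause matters**

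- If SD 7 is right, 30 per group exceeds the requirement by 30 − 17 = 13 per group. With an assumed 20% loss (24 per group) power for 7 points is still about 92%.
- If the SD actually used was near 9.5, 30 per group gives 80% with nothing spare. With an assumed 10% loss (27 per group) power is about 76%; with an assumed 20% loss (24 per group) it is about 70%.

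**The case against.** The strongest defence is that the discrepancy runs in the safe direction. On the printed inputs the trial has more power than claimed, and allocation, outcome, analysis and enrolment do not depend on the sentence. That stands, and it is why this is of moderate severity and not a threat to the design.

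A second defence is that the article condenses a fuller protocol and that the planned analysis is a linear mixed model over three assessments, not a t-test. A dropout allowance or a change-score variance could sit in the full document. This stands in part: an unreported adjustment is a real possibility alongside a misreported input. It does not cure the paragraph, which presents 30 as the minimum that follows from the four figures it prints. The single adjustments that come close would also be unusual: about 43% dropout, or a correlation between visits near zero.

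Two stronger readings are tempting and are not supported. A reader might infer that the trial is underpowered because the SD was really about 9.5; the article gives no evidence for that value, which is only what 30 would imply if the other inputs are right. A reader might also object that at 30 per group and SD 7 an observed difference of about 3.6 points (2.002 × 7 × √(2/30)) reaches significance, roughly half the important difference. That is a general feature of powered trials and not a result of this error: at 17 per group the threshold is about 4.9 points, also below 7. Nor does the article claim that significance alone shows a clinically important effect; its Statistical analysis section promises mean differences with 95% confidence intervals.

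**Conclusion.** The statement is wrong as written, with moderate severity. The printed inputs require 17 per group (two-sided t-test), not a minimum of 30, and 30 per group carries about 97% power for 7 points, not 80%. The conclusion rests on reading alpha as two-sided and the comparison as one of two independent means with SD 7 in each group; a one-sided test widens the gap.

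The documents do not show which figure is at fault or whether an adjustment was left out. What can be said is that the calculation cannot be reproduced and that the trial's margin for dropout is unknown, somewhere between ample (SD 7) and none (SD near 9.5).

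**What to change.** Keep 60 participants. Recover the inputs actually entered in the sample-size software and print them, including sidedness and any adjustment such as a dropout allowance or change-score SD.

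If the printed inputs prove to be the true ones, restate the paragraph along these lines: for a 7-point NDI difference, SD 7, two-sided 5% alpha and 80% power, 17 participants per group are required; 30 per group will be recruited, giving about 97% power for 7 points and 80% power for about 5.15 points at the same SD.

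A reason for recruiting more than 17 per group should be added only if it was part of the plan at the time; the article gives none, and one should not be supplied afterwards. The cost is one look-up and one paragraph of wording, with no change in enrolment, outcome or analysis.

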**Fig. 1 Fig1:**
[figure not shown]
Flowchart of the study

### Outcome, mediators, and timing of measures

The primary outcome of the present study will be functional disability identified through the application of the NDI. In turn, the secondary outcomes will be the intensity of pain during rest and active movement of the neck, using the Numerical Pain Scale (NPS), catastrophizing, kinesiophobia, using the pain catastrophizing scale (PCS) and Tampa Scale for Kinesiophobia (TSK), functionality and disability using the World Health Organization Disability Assessment Schedule (WHODAS) and The Copenhagen Neck Functional Disability Scale (CNFDS), and perception of the global effect of the treatment using the Global Perception Scale (GPS).

Assessments will occur at three moments: after randomization, at the end of 8 weeks of the multimodal therapeutic intervention program, and after 4 weeks, at the end of the last session of the multimodal therapeutic intervention program.

### Neck Disability Index (NDI)

The NDI is a validated instrument for the Brazilian population, comprising ten questions investigating disability and neck pain. Responses are scored from 0 to 5, and the total score ranges from 0 to 50 points, based on the answers to assess the degree of disability due to neck pain. It has been previously validated and translated for the Brazilian population and reported a clinically important minimal difference of seven points out of the possible 50 for individuals with neck pain [26, 29, 30].

### Numerical Pain Scale (NPS)

The NPS is a simple scale from 0 to 10 to assess pain intensity, where 0 represents “no pain” and 10 describes the “worst pain imaginable.” The clinically significant difference was defined as 2.1 points. Pain intensity will be assessed based on the previous 7 days [31].

### Catastrophizing scale (PCS)

The PCS assesses pain-related catastrophizing and is an instrument adapted and validated for the Brazilian population. It consists of nine items scaled on a Likert scale ranging from 0 to 5 points associated with the words “almost never” to “almost always” at the endpoints. The total score is the sum of the items divided by the number of items answered, with a minimum score of 0 and a maximum of 5. There are no cutoff points, and higher scores indicate a more significant presence of catastrophic thoughts. A clinically important minimum difference of 20% of the total score was considered by the authors [32].

### Tampa Scale for Kinesiophobia (TSK)

This instrument will be used to assess fear of movement and fear of injury recurrence, validated for the Brazilian population [33]. It consists of 17 statements about pain, and the patient must indicate their level of agreement or disagreement with each statement using a 4-point scale. The final score can range from a minimum of 17 to 68 points. A higher score indicates a greater degree of kinesiophobia, suggesting that the individual is afraid to move due to neck pain. The authors considered a clinically important minimum difference to be 20% of the total score [33].

### World Health Organization Disability Assessment Schedule (WHODAS)

The WHODAS is a self-report assessment instrument developed by the World Health Organization (WHO) and designed to evaluate functionality and disability over the last 30 days. It has been translated, adapted, and validated with adequate measurement properties for Brazilian Portuguese. A Likert scale will be used for each item to define the severity of limitation, with a score of 0 denoting “no limitation” and 4 denoting “extreme limitation or inability to function.” The total score is the sum of all 12 items, where a score of 48 points represents the worst possible restriction. The clinically important minimum difference used as a reference will be 9 points [34–36].

